## Abstract

**Background:**

The vascular access preservation and the maintenance of a complication-free fistula remains an Achilles’ heel of hemodialysis in chronic kidney patients due to its substantial contribution to the morbidity and mortality. Systematic studies in the area of examining cannulation practices, achieving complication-free cannulation, and strategies to improve fistula survival are needed. For this reason, we consider it essential to create and investigate new methodologies for approaching fistula in patients on regular HD.

The Multiple Single Cannulation Technique (MuST) is based on the association between the rope-ladder (RL) using the arteriovenous vessel through progressive rotation, and the buttonhole (BH) since there are three specific cannulation sites for each cannulation day during the week. The MuST is simple to implement and seems to be a very promising technique in terms of patient safety. Previous studies already showed an arteriovenous fistula survival similar to RL but significantly higher than BH.

**Methods:**

This MuST study is a multicenter, prospective, non-blind, parallel-group, randomized controlled trial with the intervention group submitted to MuST and a control group undergoing the rope-ladder, up to 100 subjects for each group. Patients will be randomized 1:1 to one of two cannulation technique (CT), and the follow-up period of this study will be 12 months. Primary outcome is to evaluate the arteriovenous fistula survival rate at 12 months determined by the percentage of fistulas in use from the beginning of the study to the date of the first clinical intervention by angioplasty or vascular surgery, to maintain or restore patency (unassisted patency). Secondary outcome is to evaluate arteriovenous fistula survival rate at 12 month determined by the percentage of fistulas in use from the study start to the date of access abandonment due to dysfunction, patient abandonment, or death, treatment change modality or study end. We will also evaluate the assisted primary patency and include the following secondary outcomes associated with the cannulation technique: Infection, Hematoma, Aneurysm development, and pain.

**Discussion:**

The study will investigate whether fistula survival can be improved when using cannulation by MuST compared to the RL. MuST study will provide important information on fistula survival when cannulated by MuST but also information related to its use in fistulas previously cannulated by other CTs.

**Trial registration:**

ClinicalTrials.gov identifier NCT05081648 registered on 18 October 2021.

## Background

Despite technological advances in the treatment of chronic kidney disease (CKD), vascular access (VA) remains one of the main causes of comorbidities and hospitalization of hemodialysis (HD) patients [1, 2]. A functioning VA guarantees the efficiency of the treatment and represents the lifeline for these patients. In a systematic review, Casey et al. [3] concluded that patients on HD have an increased vulnerability, not only due to their underlying chronic disease, but also as they must maintain a functioning VA. Bodily intrusion fear of cannulation, disfigurement, threat of complications, potential VA failure and difficulty sleeping are some of the concerns expressed by patients. For some patients, the fear of cannulation is an impediment to the construction of a VA or leads treatment refusal [3].

Another serious complication potentially related to cannulation techniques is local infection of the VA or bacteremia. This complication has been found to be associated with the buttonhole cannulation (BH) technique [4, 5]. However, a meta-analysis performed by Chong Ren et al. [6] failed to demonstrate this increase in prevalence, due to heterogeneity of results.

Two systematic literature reviews and a meta-analysis [6–8] did not find conclusive results when comparing the rope-ladder (RL) and BH with relation to the bleeding time reduction, hematoma, hospitalization, interventions, or VA survival. According to the authors, these limitations are associated with the studies` poor quality and heterogeneity.

The VA is often described as a lifeline [9] that enables chronic kidney patients undergo HD as a replacement therapy for renal function, enabling their survival and maintainence of an acceptable quality of life. The health, safety, and well-being of the patient must be ensured when providing care. In this way, risks must be identified, monitored and, whenever possible, prevented. Successful cannulation of a VA depends on the choice of cannulation technique (CT), environmental influences, the skill of the nursing staff, practical experience, but also on the talent, confidence, and commitment of the caregiver. The arteriovenous fistula (AVF) CT is an invasive procedure and is not free from complications but should be performed in a way that does not cause further damage or injury beyond that resulting from the essential act of clinical intervention.

However, VA preservation and the maintenance of a complication-free AVF remains an Achilles’ heel [9, 10] due to its substantial contribution to the morbidity and mortality in this patient population. Thus, demanding studies in the area of examining cannulation practices, achieving complication-free cannulation, and strategies to improve AVF survival are needed [11].

MuST is a novel Multiple Single Cannulation Technique (MuST) [12] that is based on the association between the RL by using the arteriovenous vessel through progressive rotation and the BH. This cannulation technique uses three specific cannulation sites for each day during week, allowing the cannulation sites to heal during cannulation.

In a previous randomized controlled trial (RCT) published by Peralta et.al., three cannulation techniques (CT) MuST, RL and BH have been compared by using fistula not previously used by other CT [13]. The trial was conducted in 18 clinics that recruited 172 patients randomly assigned to three different cannulation techniques. The primary endpoint was AVF primary patency at 1 year. The results showed that MuST is simple to implement and seems to be a very promising technique in terms of patient safety [13, 14]. Moreover, a significantly higher AVF survival rate compared to the BH technique could also be shown in this trial.

Therefore, the aim of the MuST study is to investigate whether new methodologies of cannulation improve fistula survival in patients on regular HD.

With the MuST Study, we are going to use fistulas previously used by traditional CT. In addition to evaluating AVF survival, we intend to evaluate other secondary outcomes not evaluated in the previous study.

## Methods

This study is a multicenter, prospective, non-blind, parallel-group, randomized controlled trial with the intervention group undergoing MuST procedure and a control group undergoing the RL technique. Patients will be randomized 1:1 to one of two CT, MUST or RL, and the follow-up period of this study will be 12 months. For each treatment group up to 100 patients are planned to be included.

## Study Objectives

The aims of the MuST Study are to:Determine the AVF survival of patients submitted to MuST compared to those submitted to RL.Determine the AVF complication rate of patients submitted to MuST compared to those submitted to RL.Analyze the intensity of pain perceived by the patient with each cannulation technique under study.

### Study hypotheses

This study examines the following hypotheses:- Does MuST allow 10% rate of greater AVF survival in patients on a regular HD program in private HD clinics than RL?- Does MuST have a lower AVF complication rate in patients on a regular HD program in private HD clinics than RL?- Do patients submitted to MuST perceive less pain than patients submitted to RL?

### Study population

#### Recruitment of the study population

Patients with end-stage kidney disease (ESKD) on a regular HD program will be recruited in 3 private dialysis clinics operating in Portugal. Decision on a study participation is made by the patient. The treading physician will inform the patient about the study and provides written information. If the patient is not willing to participate in the study by giving its written informed consent, the patient cannot be included in the study.

The patients who signed the informed consent and meet the inclusion and exclusion criteria, will be randomly organized into two groups – intervention and control groups. Each group will be stratified according to the following criteria: diabetes and AVF vintage to ensure that these variables is properly represented in the sample and avoid bias*.*

#### Inclusion criteria

Patients with AVF will be selected when:Are on a regular HD program with three weekly sessions;AVF has been in use for at least 8 weeks without incident;AVF with blood flow (Qa) ≥ 500 mL/min evaluated by thermodilution;AVF paths allow cannulations along the entire length of the vein with at least 6 cm of distance between bevels, or two distinct areas of 3 cm in length;Adult patients

### Exclusion Criteria

Patients with the following characteristics will be excluded:Those who decline to take part;Those who have undergone angiography or surgical intervention in the last 4 months in the AVF in use;Those who have undergone three or more interventions in the AVF in use;Those with use of anesthetic creams at cannulation sites.

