### Study Outcomes

#### Primary outcome

As a primary indicator, we consider AVF survival rate at 12 months and determined by the percentage of fistulas in use from the time-zero of study enrollment to the date of the first clinical intervention by angioplasty or vascular surgery, to maintain or restore patency – "unassisted patency" [15, 16].

To assess the variable "AVF survival" we consider the following criteria:- Fistula that is successfully cannulated with two needles, arterial and venous, that allows a prescribed blood flow of at least 300 mL/min and that allows for an adequate treatment will be considered a functioning AVF [17];- Fistula used without success will be considered a dysfunctional AVF, whether it has patency or not [15];- It will be considered AVF abandonment on the day that access is considered permanently unusable or not suitable for cannulation [17];

Referral for endovascular intervention [15, 16] will be based on two of the following factors of AVF dysfunction:- Decreased AVF blood flow (Qa) (assessed by thermodilution and <400 mL/min);- Increased hemostasis time (>10 min);- Cannulation failure: failure or inability to insert dialysis needles [17];- Decreased dialysis efficacy: low HD dose, *sp*Kt/V <1.2 [17] or substitution volume <21L. A parameter to quantify the HD adequacy (*sp*Kt/V) will be calculated based on ionic dialysance obtained by the integrated module Online Clearance Monitor (OCM®) from the 5008 CorDiax machine, and “*V*” was derived from total body composition assessment with a bioimpedance device (Body Composition Monitor - FMC) [18];

Or changes in the physical examination (changes in thrill, abnormal development of aneurysm, or progressive increase in edema in the AV limb) and plus one of the factors described above.

Referral for surgical intervention [15] will be based on one or more indicators of AVF dysfunction:- Rupture of the AVF wall;- AVF thrombosis;- Progressive development of aneurysm;- Acute bleeding: AVF bleeding requiring surgical intervention;- Local infection of the AVF;- Deficient distal perfusion with signs of ischemia.

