### Outcome parameters

For the sample characterization, we will describe the sociodemographic characteristics, comorbidities and laboratory data immediately before the start of the study (baseline). We will also describe the interventions already carried out in active AVF within the last year (T0).

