### Statistical analysis

Data will be analyzed according to the “intention-to-treat” [15]. The continuous variables of the “baseline” will be expressed through measures of location, dispersion and the categorial variables will be summarized using absolute and relative frequencies. Descriptive comparisons and tests will be performed between groups at baseline, at 6 and 12 months. To compare two groups by continuous variables, parametric tests will be used, namely the t-test, or nonparametric tests if normality is not assumed.

To analyse relationship between categorical variables, the Chi-square test (χ^2^) will be conducted, or Fisher’s exact test when appropriate.

The primary factors to assess fistula survival will be calculated over time from baseline to time requiring intervention (no patency assistance) or withdrawal from the study. In this case we will use the Kaplan–Meier survival curves.

For secondary factors, such as the frequency of hematoma, signs of infection, local infection or bacteremia, and thrombosis, the number of events per 1000 days of AVF will be calculated [16].

Results will be considered significant when *p* < 0.05. All the statistical analysis will be performed using SPSS (version 23; IBM, Armonk, NY, USA).

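### Earlier fistula interventions are capped over the fistula's lifetime at entry but described only for the last year, and the article's primary analysis does not use them

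*Protocol article*

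**What the plan says.** All references are to the protocol article.

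- **Exclusion Criteria.** Two rules concern earlier interventions. One has a time window: "Those who have undergone angiography or surgical intervention in the last 4 months in the AVF in use". The other has none: "Those who have undergone three or more interventions in the AVF in use".
- **Inclusion criteria.** A further condition on recent history is "AVF has been in use for at least 8 weeks without incident". If this means the most recent 8 weeks, it lies inside the 4-month window and does not narrow the intervention history further.
- **Outcome parameters.** For the baseline description: "We will also describe the interventions already carried out in active AVF within the last year (T0".
- **Recruitment of the study population.** "Each group will be stratified according to the following criteria: diabetes and AVF vintage". Earlier intervention is not among the factors.
- **Primary outcome.** Time runs "from the time-zero of study enrollment to the date of the first clinical intervention by angioplasty or vascular surgery", and the result is labelled unassisted patency.
- **Statistical analysis.** Fistula survival is "calculated over time from baseline to time requiring intervention (no patency assistance) or withdrawal from the study", shown by Kaplan-Meier curves. No covariate is named.

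**The concern.** The entry rule and the baseline description use different windows. Entry counts interventions over the fistula's lifetime and admits 0, 1 or 2. The description covers one year, of which the last 4 months are empty by design, so it shows only interventions from about 4 to 12 months before entry. A fistula with two angioplasties 14 months ago would be described like one never treated.

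This history deserves attention because an earlier intervention is the same kind of event as the primary endpoint. It is reasonable to expect a fistula that has already needed one to be more likely to need another, although the article does not say so and gives no reason for the cap. A chance difference between arms in the share of previously treated fistulas could then move the observed difference in the primary outcome, and a reader of the baseline table would see only part of it.

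The label raises a second, descriptive issue. The article separates unassisted from assisted patency as its primary and secondary patency outcomes. Some fistulas counted under the unassisted label will have been assisted before time zero. That also matters when the 12-month rate is set beside the earlier trial described in the Background, which enrolled fistulas that other techniques had not yet used.

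**Working it through.** **The plan's own figure.** The point rests on no calculated figure in the article. The size of up to 100 per arm cannot be reproduced, because no control rate or power is stated. It serves below only as an input.

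**What the windows show together**

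| Last earlier intervention | Admitted? | Seen in the one-year description? |
|---|---|---|
| Within 4 months | No | Not applicable |
| 4 to 12 months ago, 1-2 in total | Yes | Yes |
| More than 12 months ago, 1-2 in total | Yes | No |
| Any time, 3 or more in total | No | Not applicable |

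The third row is the gap. The article does not say how many fistulas fall in it.

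**Size of chance imbalance.** With share q previously treated and 100 per arm, the SD of the between-arm difference is sqrt(2 × q × (1 − q) / 100). The values of q are assumptions.

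- q = 0.20: sqrt(2 × 0.20 × 0.80 / 100) = 0.057
- q = 0.30: sqrt(2 × 0.30 × 0.70 / 100) = 0.065
- q = 0.40: sqrt(2 × 0.40 × 0.60 / 100) = 0.069

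The 95% limits at 20% and 40% are 1.96 × 0.057 = 0.11 and 1.96 × 0.069 = 0.14.

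**Effect on the observed difference.** Assume 12-month intervention risks of 35% in previously treated and 15% in untreated fistulas, a gap of 0.20.

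- 1-SD imbalance at q = 0.30: 0.065 × 0.20 = 0.013, or 1.3 points.
- 2-SD imbalance at q = 0.30: 0.13 × 0.20 = 0.026, or 2.6 points. That is about a quarter of the 10% in the first study hypothesis, if that is read as 10 percentage points.
- 2-SD imbalance at q = 0.20 and 0.40: 2 × 0.057 × 0.20 = 0.023 and 2 × 0.069 × 0.20 = 0.028.

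For scale, the overall risk on these assumptions is 0.3 × 0.35 + 0.7 × 0.15 = 0.21. The standard error of the difference is sqrt(2 × 0.21 × 0.79 / 100) = 0.058. A 2-SD imbalance therefore shifts the estimate by 0.026 / 0.058 = 0.45 standard errors. This variation is already part of the random error that a valid test allows for.

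**Effect on the test.** 6,000 trials were simulated per scenario: 100 per arm, 12 months, exponential hazards, no drop-out. A log-rank test ignoring the history was compared with one stratified by it (0 versus any). Assumed inputs were an overall control intervention-free rate of 70%, a treatment hazard ratio of ln 0.8 / ln 0.7 = 0.63 (about 80% intervention-free under MuST), and two-sided testing at 5%.

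| Previously treated | Hazard ratio for history | Type I error: ignored / stratified | Power: ignored / stratified |
|---|---|---|---|
| 20% | 1.5 | 0.047 / 0.047 | 0.371 / 0.371 |
| 20% | 2 | 0.052 / 0.052 | 0.375 / 0.380 |
| 20% | 3 | 0.054 / 0.053 | 0.351 / 0.368 |
| 40% | 1.5 | 0.052 / 0.052 | 0.369 / 0.375 |
| 40% | 2 | 0.052 / 0.053 | 0.365 / 0.370 |
| 40% | 3 | 0.052 / 0.050 | 0.345 / 0.367 |

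The simulation error of a 5% rate is sqrt(0.05 × 0.95 / 6000) = 0.003, so no type I error here is distinguishable from 5%. The largest power gain is 0.367 − 0.345 = 0.022. The simulated 95% limit for imbalance was 0.11 at 20% prevalence and 0.13 to 0.14 at 40%, matching the formula.

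**The case against.** The case against making much of this is strong, and most of it stands.

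- **The endpoint is explicit.** A reader might infer that treated fistulas are passed off as untreated in the primary outcome. The text does not support that. The clock starts at enrolment, the event is the first intervention afterwards, both arms are handled alike, and nothing is claimed about earlier history. The Background says openly that fistulas already in use will be studied. Only the label is loose.
- **The history must be established anyway.** A reader might also infer that imbalance could be neither detected nor corrected. But sites can apply the lifetime cap only by counting all interventions at screening. The one-year window governs what is described; the article does not say that nothing else is kept. What remains is that a screening count is not yet a reported baseline variable.
- **Most of the history is not necessarily hidden.** The shifts computed above concern all previously treated fistulas. Those treated 4 to 12 months before entry remain visible, so the hidden part is smaller by an amount the article does not let us calculate.
- **Covariates often belong to the analysis plan**, which is not shown. Their absence from the article is not in itself a fault. The baseline window and the endpoint label, however, are fixed in the article.
- **Stratification factors must be few** at 100 per arm. Leaving this one out is a defensible choice, and fistula vintage may capture part of the history, though an old fistula may be untreated and a younger one treated twice.

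**Conclusion.** The point holds as a small one about reporting and precision. The one-year baseline description is narrower than the lifetime rule that decides entry, so fistulas whose interventions are all older than a year look untreated in it. A plausibly prognostic history goes unused in the analysis as the article states it, and the endpoint label does not fit every fistula admitted.

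It is tempting to conclude that the primary comparison is biased. It is not: randomisation balances the history in expectation, and type I error stays at about 5%. The cost is at most about 2 points of power, together with a chance imbalance of up to roughly 11 to 14 points in 95% of trials, part of which a reader could not see.

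These sizes rest on assumed prevalences, risks and hazard ratios, none of which the article gives. That earlier intervention is prognostic is likewise an assumption. The mismatch of windows and the looseness of the label follow from the text alone.

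**What to change.** 1. In Outcome parameters, replace the one-year window with all interventions in the fistula in use, giving their number and the date of the last.
2. Prespecify earlier intervention (0 versus 1-2) as a covariate in the primary between-arm comparison, in the article's Statistical analysis section or in the analysis plan if it is not already there.
3. Describe the primary endpoint as intervention-free survival from enrolment, because some fistulas will have been assisted before time zero.

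The cost is one extra covariate and slightly more baseline data entry, since sites must already establish the count to apply the exclusion. The eligibility rules need not change, and no additional stratification factor is required.

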### Intervention

For the study implementation, the key VA person and the principal investigator in each clinic will be involved and the following procedures will be carried out:Identification of all patients with AVF;Selection of eligible patients;Informing potential participants about the study and requesting informed consent;Participants’ randomization in a 1:1 ratio, according to MuST versus RL. Randomization will be performed centrally by the project manager and electronically using random sequence generator, two branches (columns) from RANDOM.ORG.

The key VA person and the nurse’s team will be carried out the following steps:Collect AVF photo, before the start of the study (baseline), at 6 months and at 1 year during the study;MuST cannulation technique – select and identify cannulation sites with a dermographic pen until their location is easily visible due to skin depigmentation; Two areas of arterial and venous cannulation will be created, with three cannulation points each at least 1 cm apart;Rope-ladder cannulation technique – create a diagram of the cannulation sites’ orientation. The diagram will be attached to each patient’s dialysis file for quick reference;AVF physical examination before each HD treatment with recording of the findings;The daily results of each patient’s assessment will be recorded using the computer tool VASACC (vascular access) and on an Excel spreadsheet;The nurse who performs the cannulation will assess the intensity of pain perceived by the patient;Pain will be assessed immediately after cannulation of the arterial and venous area according to the 10 cm long visual analog scale (VAS) which has the classification “No Pain” on the far left and “Extreme Pain” on the right [4, 17, 21];Whenever there is a referral to the Vascular Access Center (VAC) for angiography or vascular surgery, a record will be made in the patient’s clinical file in the EUCLID database;After the intervention in the VAC, a record of the intervention per patient will be made in the Vascular Access OnLine database (AV OnLine). This registration will be performed by the nephrologist or vascular surgeon, depending on which intervention is performed. This information will then be transcribed into the Excel data collection Spreadsheet;Patients will be followed until access thrombosis, abandonment due to AVF dysfunction or surgical intervention with anastomosis alteration, patient abandonment from the study, transfer to another clinic, hospitalization, death, change of treatment modality or study end;For the variable pain intensity, time to hemostasis, peri-needle bleeding, Qa, dialysis dose (*sp*kt/V) and substitution volume will be evaluated at 3 time periods only: before study start, at 6 months, and at 12 months;Presence of scab at the cannulation site and the ease of identifying the cannulation site will be evaluated at the same time periods, but only for CT MuST;Monthly meetings will be held with the head nurse and key VA person, and additional meetings whenever necessary. All situations deviating from normality there will be discussed. Verification and collection of data.

In this clinical trial, we use a new fistula approach, because of which it is necessary to carry out training and raise awareness of nurses to assess and record the variables under study. Thus, it is not possible to blind the participants nor the nurses who perform the intervention.

Physicians performing angioplasty or vascular surgery will not be aware of the selected patients.

We will involve more than forty nurses, more than two hundred patients and ultimately, this can lead to improved evidence on fistula preservation.

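### The follow-up rule, the primary event and the analysis wording do not fit together, so the status of fistulas lost to thrombosis or abandonment without an intervention is unclear

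*Protocol article*

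**What the plan says.** Three places in the protocol article bear on when the primary outcome occurs.

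- **Primary outcome** (and the Methods part of the Abstract): fistula survival runs from enrolment "to the date of the first clinical intervention by angioplasty or vascular surgery, to maintain or restore patency". Thrombosis and abandonment are not named as events. The same section classifies failed fistulas, "Fistula used without success will be considered a dysfunctional AVF, whether it has patency or not", and dates abandonment, "It will be considered AVF abandonment on the day that access is considered permanently unusable or not suitable for cannulation", but says of neither whether it ends unassisted patency.
- **Intervention** (follow-up rule): "Patients will be followed until access thrombosis, abandonment due to AVF dysfunction or surgical intervention with anastomosis alteration". The sentence continues with exits of another kind: "patient abandonment from the study, transfer to another clinic, hospitalization, death, change of treatment modality or study end". The list does not separate failures from censoring reasons.
- **Statistical analysis**: the Kaplan-Meier time runs "from baseline to time requiring intervention (no patency assistance) or withdrawal from the study". Thrombosis is named in this section only among the secondary events to be expressed per 1000 fistula-days.

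Abandonment is named as an end date only under Secondary outcome, for assisted primary patency.

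**The concern.** A fistula that is abandoned without any procedure has no date of first intervention. Nor has one that clots and is not rescued. Under the follow-up rule both patients leave observation, and nothing in the primary definition makes that exit an event. A clotted fistula that is rescued has its intervention after the follow-up rule has already ended observation.

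If these exits are coded as censored, the censoring is informative. Kaplan-Meier assumes that a censored fistula has the same future prospects as one still in use, whereas these fistulas have just failed. Estimated patency then rises in each arm. The effect on the comparison depends on how often each arm fails in this way. The arms could differ, because the cannulating nurses are unblinded and the referral criteria include findings made at the dialysis session.

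The event date is also unsettled: Primary outcome uses the date of the procedure, and Statistical analysis uses the time at which one is required.

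**Working it through.** **No figure to reproduce.** The article states no patency, thrombosis or abandonment rate, and no event count or power. The check therefore compares the rules first and then shows what the mismatch could cost under stated assumptions.

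**Rules side by side, for a fistula with no earlier intervention**

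| Course of the fistula | Primary outcome | Intervention section | Statistical analysis |
|---|---|---|---|
| Abandoned for dysfunction, no procedure | no event date | follow-up ends | not clearly covered |
| Thrombosis, not rescued | no event date | follow-up ends | could count as requiring intervention |
| Thrombosis, then rescued | event at the procedure | follow-up ended before it | could count from the thrombosis |
| Surgery altering the anastomosis to maintain or restore patency | event | follow-up ends | event |

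The last row is consistent. The first three are not.

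**Size in one arm.** Assume constant cause-specific hazards. Let S be the true 12-month proportion free of any such failure or intervention. Let s be the share of first failures that are thrombosis or abandonment without an earlier intervention. The total hazard over 12 months is -ln S. Censoring the share s leaves (1 - s)(-ln S), so Kaplan-Meier estimates exp[(1 - s) ln S] = S^(1-s).

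| True S (assumed) | s = 10% | s = 20% | s = 30% | s = 40% |
|---|---|---|---|---|
| 0.70 | 0.725 | 0.752 | 0.779 | 0.807 |
| 0.80 | 0.818 | 0.837 | 0.855 | 0.875 |

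The overstatement runs from 1.8 points (0.80^0.9 = 0.818) to 10.7 points (0.70^0.6 = 0.807). If every such failure counts as an event, s = 0 and the bias is zero.

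**Size of the comparison.** Study hypotheses asks about 10% greater survival without saying whether that is absolute or relative. Taking it as 10 points, assume true patency of 0.70 with rope-ladder and 0.80 with MuST.

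| Share s, rope-ladder / MuST | Estimates | Difference |
|---|---|---|
| 0 / 0 | 0.700 vs 0.800 | 10.0 points |
| 30% / 30% | 0.779 vs 0.855 | 7.6 points |
| 30% / 10% | 0.779 vs 0.818 | 3.9 points |
| 10% / 30% | 0.725 vs 0.855 | 13.0 points |

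With equal shares the factor (1 - s) cancels, so the hazard ratio stays at ln 0.80 / ln 0.70 = 0.626. With 100 per arm, expected events fall from 100 × (0.30 + 0.20) = 50 to 50 × 0.7 = 35. Schoenfeld power at two-sided 5% falls from 38% to 28%.

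**The case against.** The strongest reply is that the article never says these failures are censored. The follow-up rule is an operational list of when observation stops. It also has to serve the secondary outcome, which runs past the first intervention to abandonment. It includes surgery altering the anastomosis, which is ordinarily a primary event if done for patency, so stopping follow-up cannot simply mean censoring. Other wording favours counting: the measure is fistulas in use, "Referral for surgical intervention [15] will be based on one or more indicators of AVF dysfunction" introduces a list that contains thrombosis, and the analysis time is "calculated over time from baseline to time requiring intervention (no patency assistance) or withdrawal from the study". Interventions at the Vascular Access Center are transcribed to the study spreadsheet, so a rescue after thrombosis would probably be on record. Finally, this is a condensed article, and event coding is commonly left to an analysis plan.

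Much of this stands. A reader might infer that the protocol censors its worst failures. The text does not support that as a statement of fact: the censoring is a consequence of literal reading, and thrombosis has a route to being counted. The reply does not remove the mismatch, though. The favourable reading dates failure by need while Primary outcome dates it by procedure, so it confirms that two definitions coexist. It also gives no clear place to abandonment without a procedure. And rules that are stated and disagree are not a detail left to another document.

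**Conclusion.** The point holds as an inconsistency in the definition of the primary endpoint. It is firmest for abandonment without any procedure and weaker for thrombosis. If such failures are censored, 12-month patency is overstated in each arm by about 2 to 11 points, given assumed true patency of 70 to 80%, assumed shares of 10 to 40%, and constant hazards. If they are counted, the bias is zero. The direction of any effect on the difference between arms cannot be settled from the article.

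Three stronger readings are not supported:

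- **That the result would change sign.** Hazards can be chosen to do this. Intervention at 0.20 (MuST) and 0.25 (rope-ladder) per year, with thrombosis at 0.12 and 0.04, gives a true exp(-0.32) - exp(-0.29) = -2.2 points, seen as exp(-0.20) - exp(-0.25) = +4.0 points. Nothing in the article suggests a threefold thrombosis hazard under MuST.
- **That surgery altering the anastomosis is a lost failure.** It is normally an event in its own right.
- **That surgery for every listed referral indication must count.** The stated endpoint is limited to procedures that maintain or restore patency, and the article does not say which indications qualify.

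**What to change.** Define the primary event once, as the earliest of:

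- (a) thrombosis of the study fistula;
- (b) the first endovascular or surgical intervention on it to maintain or restore patency;
- (c) its abandonment because of dysfunction.

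Date the event by that occurrence. State which of the surgical indications listed under Primary outcome fall under (b). In the Intervention section, separate these failures from the censoring reasons (withdrawal, transfer, death, change of modality, study end), and say on which side hospitalization, which stands in the same list, belongs. Use identical wording in the Abstract, Primary outcome and Statistical analysis.

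The cost is small. Abandonment and thrombosis are already outcomes that the trial tracks, and the data collection instrument has AVF intervention and Outcome sheets. The article gives only the sheet names, so the team should confirm that both dates are captured. Reported patency becomes slightly less favourable. Because this settles the primary endpoint of a registered trial, the clarification should be dated and made before outcomes are compared by arm.
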